
### Withdrawal of Individual Participants

If they wish, participants can leave the study at any time for any reason without any consequences. The investigator can withdraw a participant from the study if they consider it is in the participant’s best interests, such as avoiding delay or compromise of urgent medical care.

### Statistical Analysis

#### Sample Size Calculation

Due to the use of the Flash Mob Research design a formal sample size calculation is not possible. We assume that a number of 40 participating hospitals in Europe screening up to 50 patients each would result in a sample size of at least 2000 patients screened. This sample size should be able to answer questions about the proportion of the number of patients presenting with wearable devices and about changes in key vital signs between assessment in the hospital and a period 24 hours 1 week or 1 month previous.

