#### Data Analysis

Data will be analyzed using SPSS (version 28; IBM Statistics). All variables will be assessed for normality. This study will use basic epidemiological data to determine if patient-owned monitoring devices can be used in an emergency care setting to assess the patient’s current severity of illness and compare it with their usual state of health.

Continuous data will be analyzed using the unpaired *t* test (if the data are normally distributed) or the Wilcoxon rank sum test (if the data are not normally distributed). Changes between measurements will be described as percentage change from the first measurement taken at home before admission as the assumed baseline and as an absolute change. Categorical data will be analyzed using chi-square test. Basic statistics and descriptives will be used to identify the distribution of patient and device characteristics. Missing data will not be imputed.

Associations between the baseline measurements and the specified clinical end points and the absolute and proportional change of physiological measurements and the specified clinical end points will be assessed using linear regression and logistic regression.

Patient characteristics will be expressed as absolute numbers per (sub)category for the total patient population, the discharged patients, and the admitted patients. The heart rate and step count data will be compared for their respective average or median for the different time points. Both will be tested for significant interaction between time, disposition, and change in either heart rate or step count using a generalized linear model.

For secondary exploratory analyses, the correlation between potential outcomes will be tested using Pearson coefficient correlation analysis (*r*), where the following interpretation will be used: below 0.10 negligible, between 0.10 and 0.39 weakly correlated, between 0.40 and 0.69 moderately correlated, between 0.70 and 0.89 strongly correlated, and above 0.89 very strongly correlated. The percentile change in heart rate and step count will be calculated in comparison to the baseline, which will be assumed to be at 30 days before a hospital visit.

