## Results

Approvals have been completed in 11 sites in Denmark, 17 sites in the Netherlands, 1 site in Switzerland, and 7 sites in the United Kingdom.

The main FUSE study has gone live on the May 15, 2024, in 34 hospitals in the Netherlands (n=17), the United Kingdom (n=7), Denmark (n=9), and Switzerland (n=1). A total of 1137 patients were screened, of these, 452 patients were included and 209 patients had data on at least 2 collection points, allowing for an analysis of trends.

Preliminary analysis will be completed by December 31, 2024, and the main manuscript will be submitted for publication by the end of March 2025.

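### The planned 'at least 2000' screened is in fact a maximum, and the claim that it suffices for the change questions uses the wrong denominator and gives no precision

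*Protocol article*

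**What the plan says.** All of the planning is in the Sample Size Calculation section. It opens with a disclaimer: "Due to the use of the Flash Mob Research design a formal sample size calculation is not possible". It then takes 40 hospitals and projects the total: "screening up to 50 patients each would result in a sample size of at least 2000 patients screened". Finally it judges that size sufficient: "This sample size should be able to answer questions about the proportion of the number of patients presenting with wearable devices". The same sentence extends the judgement to changes in key vital signs between the hospital assessment and 24 hours, 1 week or 1 month before. No confidence interval, margin of error, power or ICC is given.

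The Results section reports what happened. "The main FUSE study has gone live on the May 15, 2024, in 34 hospitals", split as 17, 7, 9 and 1 across four countries, and "A total of 1137 patients were screened, of these, 452 patients were included and 209 patients had data on at least 2 collection points". It adds that this last group is the one that permits an analysis of trends.

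Two other places bear on precision. Governance asks each unit to collect data on everyone presenting in the study areas during one 24-hour period. The list of data items includes a site identifier.

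**The concern.** Three things in one short section do not fit together.

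- **The bound is reversed.** *Up to* sets a maximum per hospital and *at least* sets a minimum in total. One cannot follow from the other.
- **One number is made to serve two questions.** The screened total is the right denominator for device use. It is not the right one for changes in heart rate or steps, which need a patient who was included, owns a device and has more than one reading.
- **Adequacy is asserted without a yardstick.** Patients arrive in hospital-sized groups, each largely one day at one site. If device use varies between hospitals, the screened total carries less information about the overall proportion than the same number of independent patients would.

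At stake is how much weight a reader gives the main proportion. The article plans to contrast the device-using population with national surveys and hopes the results will aid power calculations for later studies. Both uses need a realistic interval, and the second needs an ICC.

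**Working it through.** **Inputs from the article.** Planned: 40 hospitals, 50 patients each as a ceiling, total 2000. Actual: 34 hospitals, 1137 screened, 452 included, 209 with at least two collection points.

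**Inputs assumed.** The article gives no ICC, so 0.02, 0.05 and 0.10 are used as a range. Hospitals are taken as equal in size. The proportion is set at p = 0.5, where the interval is widest.

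**Step 1: the planned figure.** 40 × 50 = 2000. The number reproduces, but only as the maximum. For the hospitals that took part, the ceiling is 34 × 50 = 1700.

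**Step 2: what was reached.** 1137 / 2000 = 56.9%, a difference of 863. The mean per hospital is 1137 / 34 = 33.4.

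**Step 3: the denominator for trends.** 209 / 1137 = 18.4% of those screened, and 209 / 452 = 46.2% of those included. At the same yield, even 2000 screened would have given about 2000 × 209 / 1137 = 368 patients with repeated data.

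**Step 4: precision of the device proportion.**

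Design effect: DE = 1 + (m − 1) × ICC, where m is the mean number per hospital.

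95% half-width = 1.96 × √(p(1 − p) / N) × √DE. Effective N = N / DE.

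With independent patients:
- N = 2000: 1.96 × √(0.25 / 2000) = 2.2 points.
- N = 1137: 1.96 × √(0.25 / 1137) = 2.9 points.

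With clustering:

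| ICC (assumed) | N = 2000, m = 50: DE | Effective N | Half-width, points | N = 1137, m = 33.4: DE | Effective N | Half-width, points |
|---|---|---|---|---|---|---|
| 0.02 | 1.98 | 1010 | 3.1 | 1.65 | 690 | 3.7 |
| 0.05 | 3.45 | 580 | 4.1 | 2.62 | 434 | 4.7 |
| 0.10 | 5.90 | 339 | 5.3 | 4.24 | 268 | 6.0 |

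**Step 5: sensitivity to p.** At p = 452 / 1137 = 0.398 and N = 1137, the half-width is 2.8 points if independent, and 3.7, 4.6 and 5.9 points at the three ICCs. The choice of p hardly matters. The value 0.398 is the rate of inclusion among those screened, not the device proportion, and serves here only as a second value of p.

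**Step 6: the trend subset.** Here m = 209 / 34 = 6.1. For a mean or proportion, DE runs from 1 + 5.1 × 0.02 = 1.10 to 1 + 5.1 × 0.10 = 1.51. In this subset, small numbers matter more than clustering.

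**The case against.** The best defence is that this is an informal projection for a feasibility study, openly labelled as not a formal calculation. The Results section gives every actual count, including the 209. Missing a recruitment projection is not a planning error, and a condensed article may leave site adjustment to an analysis plan. Much of this stands. The shortfall is not the fault here, and silence about site effects is not in itself a finding. The reversed bound and the shared denominator remain, because both are written in the Sample Size Calculation section and no further document can make them consistent.

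It can also be said that the loose word is *up to* rather than *at least*, since Governance asks units to include everyone in a 24-hour period and names no cap. That is possible, and the fix allows for it. Even so, a minimum of 2000 would then need 50 to be an average or a floor, which the text does not say.

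Three stronger readings are tempting and are not supported:

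- *That the stated precision is too favourable.* The article states no precision. Only the unquantified claim of adequacy can be criticised.
- *That every between-group test is too liberal because it ignores hospitals.* The article names simple tests, for example "Categorical data will be analyzed using chi-square test", without a site term. But it does not rule out adjustment, and its generalized linear model is left open. Moreover, admitted and discharged patients would ordinarily both occur within the same hospital. For such a contrast, ignoring a positive ICC need not make intervals too narrow and can make them too wide. The design effect above applies to an overall proportion or mean.
- *That 39.8% is the primary result.* It is included over screened, and inclusion also required consent and the absence of imminently life-threatening illness.

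**Conclusion.** The point holds in a limited form. The planned total is wrongly described: 40 hospitals at up to 50 each gives at most 2000, and 1700 for the 34 hospitals that took part. The section also credits the screened number with answering the change questions, which rest on 209 patients, 18% of the 1137 screened. Neither conclusion needs any assumption beyond reading 50 as the cap that the text makes it.

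The claim of adequacy for the device proportion is unquantified rather than wrong. With 1137 screened, the 95% half-width lies between 2.9 points (independence) and 6.0 points (ICC 0.10). This rests on assumed ICCs and equal hospital sizes. An interval of about ±6 points is still usable for a feasibility proportion, so the aim is weakened, not defeated. The change is worth making because it is cheap, but it does not put the study in doubt.

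**What to change.** 1. Restate the figure as *at most 2000 screened (40 × up to 50)*. If 50 was meant as an expected number and not a cap, drop *up to* and say so.
2. State that the heart-rate and step-count trend analyses rest on included patients with at least two time points, and give that number separately from the number screened.
3. Replace the statement of adequacy by the expected 95% half-width of the device proportion over a stated ICC range. At p = 0.5 this is about 2.2 points for 2000 independent patients and 3.1 to 5.3 for ICC 0.02 to 0.10. For 1137 it is about 2.9, and 3.7 to 6.0.
4. Report the main device proportion with a confidence interval that allows for clustering by site identifier (cluster-robust or GEE, or a random-intercept logistic model), and report the estimated ICC for use in later studies. A country fixed effect is not needed and would be awkward, because Switzerland has a single hospital and the two effects cannot be separated there.

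The cost is rewording and a standard software option. The site identifier is already collected and no more patients are needed. The downside is a wider interval for the main proportion.

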#### Data Analysis

Data will be analyzed using SPSS (version 28; IBM Statistics). All variables will be assessed for normality. This study will use basic epidemiological data to determine if patient-owned monitoring devices can be used in an emergency care setting to assess the patient’s current severity of illness and compare it with their usual state of health.

Continuous data will be analyzed using the unpaired *t* test (if the data are normally distributed) or the Wilcoxon rank sum test (if the data are not normally distributed). Changes between measurements will be described as percentage change from the first measurement taken at home before admission as the assumed baseline and as an absolute change. Categorical data will be analyzed using chi-square test. Basic statistics and descriptives will be used to identify the distribution of patient and device characteristics. Missing data will not be imputed.

Associations between the baseline measurements and the specified clinical end points and the absolute and proportional change of physiological measurements and the specified clinical end points will be assessed using linear regression and logistic regression.

Patient characteristics will be expressed as absolute numbers per (sub)category for the total patient population, the discharged patients, and the admitted patients. The heart rate and step count data will be compared for their respective average or median for the different time points. Both will be tested for significant interaction between time, disposition, and change in either heart rate or step count using a generalized linear model.

For secondary exploratory analyses, the correlation between potential outcomes will be tested using Pearson coefficient correlation analysis (*r*), where the following interpretation will be used: below 0.10 negligible, between 0.10 and 0.39 weakly correlated, between 0.40 and 0.69 moderately correlated, between 0.70 and 0.89 strongly correlated, and above 0.89 very strongly correlated. The percentile change in heart rate and step count will be calculated in comparison to the baseline, which will be assumed to be at 30 days before a hospital visit.

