**Secondary study end points**
Secondary end points will focus on four areas of interest:The difference between the heart rate at rest from the wearable device 24 hours, 1 week, and 1 month before assessment by emergency practitioners compared with the first set of vital sign parameters measured on admission to acute care.The change in daily steps taken in the month before admission to acute care.To describe the population that is wearing devices that collect data on vital signs in terms of gender, age group, severity of illness as measured by a standard set of vital signs, level of education, and digital literacy and frailty.To explore the association of changes in heart rate from the community to assessment in acute care services with clinical end points such as admission to a general ward or admission to a critical care area or discharge home within 24 hours from the time of clinical assessment.

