### Limitations

The distribution of wearables in the population might point toward the exclusion of a significant proportion of the population from this type of support: patients who are less financially well off or not sufficiently digitally or health literate might be disadvantaged in a future health care. This data will hence be collected as part of FUSE. While this study focuses on readily available data and will require in future supplementation by detailed qualitative data.

The study is conducted by a group of secondary care clinicians with expertise in medical emergencies. Many of the patients who will be screened and included will have previously presented in primary care. There is no theoretical reason that the results from this study might not be applicable to those presenting in primary care, but this might require future research.

In preparation of the study, we reviewed sales for the top 20 devices in the Dutch and British markets. For these devices, we have created a data dictionary for investigators that will enable them to assist patients in the location of relevant data. With new devices coming online and changes in consumer habits, the frequency distribution of these devices might however be soon outdated.

The study will explicitly not address the quality of data collected in wearables. We will, however, report on the distribution of devices and approval for medical use where applicable. In the same vein, we anticipate that the duration of usage by individuals will affect the measurements. This is something that we might not be able to evaluate in the current setup.

Given that patients will use a range of devices with different methods for data acquisition and different usage patterns our analysis will focus on the comparison of relative changes in parameters for individuals (intraindividual variation). This relies on the assumption that individuals will have a pattern of usage that is constant over time. Further research will be required, especially if it turns out that the variation between the collected parameters turns out to be large in the days before deterioration and presentation to the hospital.

Finally, future health care needs to be equitable. FUSE will include data that will allow us to gauge some aspects of equity, diversity, and inclusion which are crucial for the development of policy and strategy in this field.

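### Only unpaired tests, and a generalized linear model with no stated within-patient correlation, are named for heart-rate and step-count comparisons made within the same patient

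*Protocol article*

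**What the plan says.** The Data Analysis section gives one general rule for continuous variables: "Continuous data will be analyzed using the unpaired *t* test (if the data are normally distributed) or the Wilcoxon rank sum test". It names no paired t test, signed-rank test, mixed model or other repeated-measures method.

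On time points, the same section says "The heart rate and step count data will be compared for their respective average or median for the different time points", without naming a separate test. Heart rate and step count are then to be "tested for significant interaction between time, disposition, and change in either heart rate or step count using a generalized linear model". Nothing is said about correlation between repeated values from one patient. Changes themselves are to be summarised: "Changes between measurements will be described as percentage change from the first measurement taken at home before admission as the assumed baseline". Missing data are not imputed.

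The end points are within-patient. Under Secondary study end points, heart rate is "The difference between the heart rate at rest from the wearable device 24 hours, 1 week, and 1 month before assessment", set against the first value measured in acute care. Steps are "The change in daily steps taken in the month before admission to acute care". The Limitations section says that "our analysis will focus on the comparison of relative changes in parameters for individuals (intraindividual variation".

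**The concern.** The aim in the Introduction is to use each patient as their own reference. An independent-group test does not use the pairing. It keeps the between-patient variance that the design is meant to remove, so the home-to-hospital and day-to-day contrasts look less precise than they are.

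The Conclusions say that the results should help with power calculations for later studies. If a later paired study were sized from the unpaired variance, its sample size would be too large by a factor of 1/(1 − ρ), where ρ is the within-patient correlation. That factor is 2 at ρ = 0.5.

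Validity is also in question. If patients contribute to some time points and not to others, a difference between time-point means contains both change and a difference in who supplied data.

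Finally, the model sentence lists change among the interacting terms alongside time and disposition. Change is already the contrast over time in the outcome, so the model cannot be set up unambiguously from that sentence.

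**Working it through.** **Inputs from the protocol.** The Results section gives 452 patients included and 209 with at least two collection points: 209/452 = 46.2%, so 243 (53.8%) lack a second point. The Sample Size Calculation section gives 40 hospitals × up to 50 patients = 2000 screened. This reproduces, but it has no alpha, power, effect size or SD behind it, so there is no planned precision to check against.

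**Assumptions.** The protocol gives no SD, within-patient correlation or alpha. I take ρ from 0.3 to 0.7, two-sided alpha of 0.05 and a true shift of 0.2 SD. I also assume that the same 209 patients contribute to both time points with equal SD.

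**Unpaired against paired.**
- Unpaired SE = SD × √(2/209) = 0.0978 SD.
- Paired SE = SD × √(2(1 − ρ)/209).
- Ratio = 1/√(1 − ρ).
- Paired power = Φ(0.2 SD/paired SE − 1.96).
- Unpaired power = Φ((0.2 SD − 1.96 × unpaired SE)/paired SE), because the paired SE is the true one.
- Actual type I error of the unpaired test = 2(1 − Φ(1.96/√(1 − ρ))).

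| ρ | Paired SE (in SD) | SE ratio | Power, paired | Power, unpaired | Type I error, unpaired |
|---|---|---|---|---|---|
| 0 | 0.0978 | 1.00 | 53% | 53% | 5% |
| 0.3 | 0.0818 | 1.20 | 69% | 54% | 1.9% |
| 0.5 | 0.0692 | 1.41 | 82% | 55% | 0.56% |
| 0.7 | 0.0536 | 1.83 | 96% | 56% | 0.04% |

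If more patients contribute at one time point than at the other, the precision gap narrows, but the two means then come from different sets of patients.

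**Model with rows treated as independent.** A time-by-disposition linear model was simulated with 209 patients, about half admitted, equal within-patient correlation and 1500 runs per setting. At ρ = 0.5:

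| Contrast | Model SE / true SE, 4 time points | Type I error, 4 time points | Model SE / true SE, 3 time points |
|---|---|---|---|
| Time | 1.42 | 0.6% | 1.42 |
| Time × disposition | 1.43 | 0.5% | 1.39 |
| Disposition at one time point | 1.02 | 4.1% | 1.01 |
| Disposition averaged over time | 0.64 | 21.6% | 0.71 |

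The time and time-by-disposition contrasts, which the plan does name, are conservative. Only a disposition effect pooled over repeated rows is anti-conservative. Its type I error runs from 14% to 26% over ρ = 0.3 to 0.7 with 3 or 4 time points.

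**The case against.** The rule on continuous data is general and is not expressly tied to the home-to-hospital change. Changes are to be described as absolute and percentage values per patient, which does form within-patient differences. Patients are also split into discharged and admitted, and unpaired tests are right there. Linear or logistic regression of one change value per patient on a clinical end point is valid as well. The article says generalized linear model without stating or ruling out a correlation structure. GEE is one way to fit such a model, and covariance details are often left to a fuller document.

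Most of this stands and limits the point. It does not remove it: heart rate and steps are to be compared across time points, and the only tests stated for continuous data are for independent groups. That is something the article fixes, not something it omits.

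A reader might go further and infer that standard errors are wrong in both directions, with false-positive rates well above 5%. The protocol does not support that. Inflation needs a disposition effect pooled over repeated rows, which is not among the tests it names. Nor does it say that the model ignores the clustering; it is simply silent.

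**Conclusion.** The point holds in a limited form. For same-patient comparisons over time, the protocol names only independent-sample tests, and a model whose handling of repeated values is unstated and whose interaction is badly worded. Followed as written, the time-point contrasts lose precision: standard errors about 1.2 to 1.8 times too large, and power of 54% to 56% instead of 69% to 96% for a 0.2 SD shift in 209 patients. They can also mix change with differences in who has data.

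These sizes rest on the assumed correlation of 0.3 to 0.7 and on all 209 patients contributing to the contrast. The protocol does not say that their two collection points are a home and a hospital heart rate. Home against hospital applies to heart rate only; steps have no hospital value and are compared day against day. The end points concerned are secondary, and the primary outcome (device proportion, recruitment and retention) is untouched. The correction is worth making but does not threaten the study's main result.

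**What to change.** In the Data Analysis section:

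- Name the paired t test or the Wilcoxon signed-rank test for each time-point contrast: home against first hospital value for heart rate, day against day for steps.
- Keep the unpaired t and rank sum tests for admitted versus discharged patients.
- For time by disposition, state a linear mixed model with a patient random effect, or GEE. Use heart rate or step count as outcome, and time, disposition and their interaction as terms. Put steps on a scale that allows zero-step days.
- Remove change from the list of interacting terms.
- Report how many patients contribute to each time point and to each pair.

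A mixed model or GEE also uses patients with only some time points. The cost is a change of wording and, where analyses have already been run, a rerun with standard procedures. No new data are needed.

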#### Secondary Outcome Measures

Secondary outcomes measures include measures of epidemiology and physiology:

We will report trends for heart rate and step count, specifically the difference between the heart rate at home 24 hours, 1 week, and 1 month before clinical assessment from the wearable device compared with the first vital signs measured on admission to acute care as both an absolute and a proportional change.

We will also describe the degree of association between changes to vital signs from the community to assessment in acute care services with admission to a general ward or admission to a critical care area or discharge home within 24 hours from the time of the first hospital assessment.

The population wearing or carrying devices will be described in terms of gender, age, ethnicity, level of education, and digital literacy and contrasted with data from national surveys.

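### Relative step change divides by one home measurement although seven daily values are recorded; means and regressions on it suffer, and a multi-day baseline is a cheap repair

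*Protocol article*

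**What the plan says.** All places are in the protocol article.

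- **Change measure.** Data Analysis: "Changes between measurements will be described as percentage change from the first measurement taken at home before admission as the assumed baseline". The same sentence goes on to add a second scale: "as the assumed baseline and as an absolute change".
- **Summary and tests.** Data Analysis: "The heart rate and step count data will be compared for their respective average or median for the different time points". Variables are checked for normality, and the non-normal alternative is a rank test: "or the Wilcoxon rank sum test (if the data are not normally distributed".
- **Regressions.** Data Analysis says that associations of "the absolute and proportional change of physiological measurements and the specified clinical end points will be assessed using linear regression and logistic regression". A generalized linear model is also planned for the interaction of time, disposition and change in heart rate or step count.
- **Emphasis.** Limitations: "our analysis will focus on the comparison of relative changes in parameters for individuals".
- **Secondary outcomes.** Changes are reported "as both an absolute and a proportional change", but that sentence spells this out for heart rate only.
- **Second baseline.** The last paragraph of Data Analysis places the baseline for change in both heart rate and steps at 30 days before the hospital visit.
- **Data collected.** The list of data items under Study Procedures records daily walking, as steps or as distance, for the 7 days before presentation. No earlier step data are listed.

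**The concern.** Daily step counts vary a lot within one person and can be very low or zero in frail or ill patients. A percentage change puts one such day in the denominator. It cannot fall below -100%, has no upper limit, and does not exist when the baseline day is zero. A low baseline day produces a very large apparent rise, and a high one a bounded fall, so random variation does not cancel out.

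Two things are at stake. First, if individual percentage changes are averaged, a real loss of mobility before admission can look smaller than it is. Second, when the same quantity is a regression predictor, a few patients with low baselines carry much of its variation and the association with disposition becomes harder to detect. The Conclusions section says the results should aid power calculations for later studies, so a distorted or noisy estimate would carry forward.

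**Working it through.** The document gives no mean, SD or expected change for steps, so there is no planned figure to reproduce. The only input from the document is the 209 patients with data on at least two collection points (Results). All other values are assumptions.

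**1. Mean of individual percentage changes.** Let the baseline day X0 and follow-up day X1 be independent and log-normal within a person, with within-person log SD s and true ratio r. The log ratio has variance 2s², so E[X1/X0] = r·exp(s²), and the mean percentage change is 100·(r·exp(s²) − 1).

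| s | exp(s²) | no change (r = 1) | 30% fall (r = 0.7) | halving (r = 0.5) |
|---|---|---|---|---|
| 0.4 | 1.174 | +17% | -18% | -41% |
| 0.5 | 1.284 | +28% | -10% | -36% |
| 0.6 | 1.433 | +43% | 0% | -28% |
| 0.7 | 1.632 | +63% | +14% | -18% |

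If days have correlation ρ on the log scale, the exponent becomes s²(1 − ρ). With ρ = 0.5 and s = 0.5, exp(0.125) = 1.133, so +13% instead of +28%.

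**2. What the other planned summaries show.** Simulation with n = 209, a true fall of 30%, baseline median 5000 steps, between-person log SD 0.6 and no zero days. The mean percentage change was at or above zero in 2.5% of samples at s = 0.5, 50% at s = 0.6 and 93% at s = 0.7. In the same samples the median percentage change stayed at about -30%. The mean absolute change was about -2030 to -2300 steps and never reached zero.

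**3. Regression on disposition.** Simulation with n = 209, half admitted, true falls of 40% (admitted) and 20% (discharged), the same step distribution and no zeros. Power of logistic regression with each form of change as predictor:

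| s | absolute, one day | percentage, one day | percentage, three-day mean baseline | log ratio, one day |
|---|---|---|---|---|
| 0.4 | 60% | 90% | 99% | 95% |
| 0.55 | 37% | 60% | 79% | 75% |
| 0.7 | 21% | 32% | 51% | 53% |

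The columns come from two runs; where both gave the one-day percentage figure, they differed by at most 3 points. Across these values of s, ten of the 209 patients supplied 47% to 68% of the sum of squares of one-day percentage change.

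**4. Zeros and the log ratio.** With 2% zero baseline days and 5% zero follow-up days, the log ratio is undefined for about 6.9% of patients, against 2.0% for percentage change, because a zero follow-up is a valid -100%. Adding a constant c makes the result depend on c. With 5% zero follow-up days and s = 0.5, the change is -53.5% (c = 1), -47.8% (c = 10) or -40.9% (c = 100). In the regression setting at s = 0.4, 5% zero follow-up days with c = 50 cut the power of the log ratio from 96% to 39%, while percentage change kept 87%.

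**5. Heart rate.** With an assumed 15% rise and a log-ratio SD of 0.10 to 0.25, the mean percentage change is 15.6% to 18.7%. The distortion is small.

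**The case against.** The strongest reply is that the harm needs a summary the document never fixes. It allows an average or a median, plans a rank test for non-normal data, and reports absolute change in the same sentence as percentage change. Step 2 shows that the median and the absolute change both reveal the fall. This stands for the descriptive results. A reader might infer that the trial's estimate of step change will be biased upward; the documents do not support that. The direction is not universal either. Zero follow-up days pull the mean down (from -10.1% to -19.0% at s = 0.5 with 10% zero follow-up and 2% zero baseline days). If patients with low baselines fall proportionally more, the mean percentage change can exceed the fall in the ratio of means (-28.8% against -20.7%).

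A second reply is that the regressions may concern heart rate only. The association end point among the secondary end points names heart rate, and the absolute-and-proportional wording in the secondary outcomes is spelled out for heart rate. This stands in part. However, the regression sentence speaks of physiological measurements in general, the generalized linear model names step count, and the Introduction treats mobility as a suggested vital sign.

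A third reply is that transformations and rules for zero days belong in an analysis plan that is not shown. Agreed; their absence is not the point. The choice of a single-measurement denominator is stated in the article itself.

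A reader might also infer that a log ratio settles the matter. Step 4 shows that it removes the asymmetry but handles zeros worse.

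**Conclusion.** The point holds for step counts and in limited form. Dividing by one first measurement, when seven daily values are recorded, gives a skewed individual change with no value at a zero baseline. A mean of such changes would typically be too high, by 17 to 63 percentage points with no true change under the stated assumptions, and by less with correlated days. Regressions on it lose power: under the assumed scenario, 9 to 19 points compared with a three-day baseline (99 − 90, 79 − 60, 51 − 32).

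The within-person SD, log-normality, independence of days and effect sizes are all assumed, so the sizes are illustrative; the skewness and the undefined case are not. The median and absolute change already protect the descriptive summary, and heart rate is little affected. Step change is a secondary end point in a feasibility study, so the weight is moderate. The two baseline definitions in Data Analysis conflict whatever the variance, and the 30-day one cannot be computed from the listed step data.

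**What to change.** - **Baseline.** Define the step baseline as the mean or median of the earliest several of the seven recorded days, for example the first three. Reconcile this with the 30-day baseline in Data Analysis, and use one definition throughout.
- **Description.** Summarise percentage change in steps by the median only, and keep the absolute change.
- **Regressions.** Enter the follow-up step value adjusted for that baseline. It involves no division and is defined at zero. The main gain in power comes from the multi-day baseline; the adjusted model is chosen for these properties, not for extra power.
- **Sensitivity analysis.** A log ratio may be added, with a zero rule fixed in advance, because it is also undefined at zero follow-up and depends on the constant added.
- **Units.** Walking may be recorded as steps or as distance. Percentage change is free of units, but absolute change and the adjusted model need one unit, so state how the two are handled.

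The cost is analysis wording; no new data are needed. The drawback is that the earliest recorded days may already fall within the illness, whereas the objectives refer to values while stable and well. A fall measured from those days could be understated, and this should be stated as a limitation.
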